### 4.2 SAMPLE SIZE CALCULATION

In futility studies, the direction of the hypotheses is different from that in traditional phase III efficacy or effectiveness trials. The study sample size was based on testing the *null hypothesis that Simvastatin is not futile*, in terms of the primary outcome (change in MDS-UPDRS part III motor subscale score in the OFF state at 24 months). If at the end of the study there is evidence to reject the null hypothesis, then it is unlikely that Simvastatin will be considered for a phase III study, although the final decision on planning for progression to a phase III study will be made in discussion with the trial oversight committees and other key stakeholders.

The minimum clinically important difference (MCID) in UPDRS motor score has been estimated to be between 2.3 and 2.7 points. The null hypothesis,  $H_0$ , in this futility study is that the mean change in MDS-UPDRS part III score between baseline and 24 months for the Simvastatin group is at least 3 points less (as higher MDS-UPDRS scores are worse) than the corresponding mean change in the placebo group. The alternative hypothesis,  $H_1$ , is that the mean change in MDS-UPDRS part III score for the Simvastatin group is not at least 3 points less than the corresponding mean change in the placebo group. Mathematically, this is written as

$$H_0: \mu_s - \mu_p \leq -3 \text{ versus } H_1: \mu_s - \mu_p > -3,$$

where  $\mu_s$  is the expected mean change in MDS-UPDRS part III score from baseline to 24 months for the Simvastatin group and  $\mu_p$  is the expected mean change for the placebo group.

Due to this change in the hypotheses in comparison with conventional phase III studies, the type I and type II error probabilities are interpreted differently compared to the traditional efficacy/effectiveness studies:

- A type I error occurs when the active treatment (Simvastatin) is non-futile but is rejected following the futility study, leading to an effective treatment not being considered for a phase III study (i.e. an erroneous rejection of  $H_0$ ); the probability of this occurring is denoted by  $\alpha$ ;
- A type II error occurs when the active treatment (Simvastatin) is futile but there is insufficient evidence to reject the null hypothesis of non-futility, and an ineffective treatment is considered for a phase III study (i.e. an erroneous failure to reject  $H_0$ ); the probability of this occurring is denoted by  $\beta$ .

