Hence  $\alpha$  and  $\beta$  were chosen to reflect the futility design-based hypotheses, with the one-sided  $\alpha$  set at 10% and  $\beta$  at 20% (i.e. 80% power).

Based on a recently reported study at the time of the design of this futility trial, the expected mean increase in MDS-UPDRS part III from baseline to 12 months in the placebo group is assumed to be 2.2 points, with corresponding standard deviation of 7.3 points. Assuming that this increase in MDS-UPDRS part III is linear over time, gives an expected mean increase from baseline to 24 months of 4.4 points in the placebo group (i.e.  $\mu_p = 4.4$ ). Therefore, if we assume the MCID is -3, this implies the mean of the Simvastatin group,  $\mu_s$ , is 1.4 points. Additionally, we assume a slightly inflated standard deviation over this period of 7.5 points.

The sample size calculation was based on a two-sample t-test with a 10% one-sided alpha. Following the previously listed assumptions, the number of participants needed to follow-up at 24 months (i.e. with primary outcome data) is 57 participants per group, to provide 80% power to reject the null hypothesis of non-futility and declare futility.

This sample size was inflated to allow for a proportion of participants allocated to the Simvastatin group to stop taking the trial medication during the initial 1-month low dose phase. Assuming that this proportion was 15%, the above sample size was inflated by  $(1-0.15)^{-2}$ , to give 79 participants per group. Secondly, the sample size was adjusted to allow for a (non-differential) loss to follow-up rate of 20%. Accordingly, the sample size was further inflated by a factor of  $(1-0.2)^{-1}$ , to give a sample size of 99 participants per group and a total recruitment target of 198 participants commencing the higher dose phase of the study.

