#### **4.4.2 Protocol Violation or Deviation**

Non-compliance may occur in some instances if participants do not complete their allocated treatment according to the study protocol, or if the follow-up visit was not within  $\pm 2$  weeks of the scheduled date. This could occur because of medical issues such as fatigue, deterioration of health, acceleration of PD, difficulty in attending outpatient clinics in the OFF state, or participants may simply decide that they no longer want to complete the programme.

Within the PD STAT study protocol (section 17.9), there is allowance for study drug dose alterations, depending on whether the patient is at the initial low dose phase or high dose phase. If a participant discontinues treatment during the low dose phase, attempts will be made to recruit an additional participant. During the high dose phase, participants with unwanted symptoms/side effects may reduce to the 40mg dose and then may continue on the 40mg dose for the remainder of the trial or, at the discretion of the local investigator, such participants may later be re-challenged with the 80mg dose after resolution of the unwanted symptoms. Participants who are on the 80mg dose and subsequently fulfil the trial stopping criteria will be withdrawn from treatment but invited to continue with the study assessments.

Complete identification of compliance with the study protocol may not be possible. For example, there may be unreported instances where participants miss doses of their medication or medication containers are not returned. Compliance will be assessed based on a combination of each participant's self-reported compliance during telephone calls and capsule count, but this may not capture the participant's true compliance. Therefore, we will base compliance on the reported data, acknowledging it may have limitations. Figure 1 outlines the possible forms of non-compliance we will be able to identify through the data collected.

We have constructed two definitions of study compliance. These are:

- (i) Participants are compliant only if they proceed to and maintain the 80mg dose and attend 24 month follow-up within their 2-week window of their due date, and non-compliant if they remain on the 40mg dose, discontinue trial treatment or attend the 24-month follow-up visit outside of the 2-week window.

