#### **7.3.1 Non-Compliance Sensitivity Analysis**

Frequency and percentages of non-compliers for each of the compliance definitions outlined in section 4.4.2 will be reported. If  $\geq 20\%$  of participants with 24-month outcome data are classed as non-compliers based on either compliance definition (i) or definition (ii) from section 4.4.2, a sensitivity analysis based on that definition will be triggered. Therefore, a maximum of two non-compliance sensitivity analyses will be performed.

One potential method for sensitivity analyses is a per protocol analysis, which would only analyse participants who completed the trial as indicated in the protocol. However, this approach could introduce bias by excluding participants after randomisation and thus jeopardising the group comparability achieved through randomisation.

As an alternative, a complier-average causal effect (CACE) analysis will be undertaken if triggered according to the criteria above, which will provide an unbiased estimate of the intervention effect, based on protocol compliance. In a CACE analysis, participant's allocated group is included in the model as an instrumental variable and the participant's given treatment is an endogenous variable, which will consist of placebo or intervention. The definitions of compliance in section 4.4.12 will be used to determine the participants' given treatment.

Under compliance definition (i), intervention participants' given treatment (the endogenous variable) would remain as intervention only if they proceeded to and maintained the 80mg dose and attended their 24-month follow-up assessment within the 2-week window. If they did not proceed to the 80mg dose, or if they did not attend their 24-month follow-up within the 2-week window, they would be classed as non-compliers and their given treatment would be classified as placebo.

Compliance definition (ii) is less stringent than compliance definition (i); participants in the intervention group will be classed as compliers and their given treatment will remain as intervention even if they do not proceed to the 80mg dose, provided they attend their 24-month assessment within the 2-week window and at least remain on the 40mg dose. Otherwise, their given treatment will become placebo.

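### The separate CACE triggers in SAP 7.3.1 can leave only the definition (i) analysis, which codes 40mg simvastatin as placebo and estimates the 80mg effect without bias only if 40mg has no effect

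*SAP*

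**What the plan says.** SAP 4.4.2 defines compliance in two ways. Under (i), a participant is non-compliant on remaining on 40mg, discontinuing trial treatment, or attending the 24-month visit outside the 2-week window. Under (ii), only discontinuation or an out-of-window visit counts. The same section allows a participant with side effects in the high dose phase to step down and "continue on the 40mg dose for the remainder of the trial".

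SAP 7.3.1 turns these definitions into the exposure variable of an instrumental-variable model. For definition (i), a simvastatin participant's "given treatment (the endogenous variable) would remain as intervention only if they proceeded to and maintained the 80mg dose" and the visit was in window; otherwise the participant is coded as placebo. For definition (ii), "their given treatment will remain as intervention even if they do not proceed to the 80mg dose", provided at least 40mg is continued and the visit is in window.

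If non-compliance under a definition reaches 20%, "a sensitivity analysis based on that definition will be triggered". 4.4.2 likewise takes the definitions in turn. The CACE is described as an analysis "which will provide an unbiased estimate of the intervention effect, based on protocol compliance", and the end of 7.3.1 has it interpreted by the one-sided futility test. Where a trigger is not met, 7.3 provides descriptive statistics by compliance.

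**The concern.** A CACE estimate divides the difference between the randomised arms by the share of the simvastatin arm coded as treated. This is valid only if allocation has no effect on the outcome of people whose coded exposure it does not change (the exclusion restriction). A simvastatin participant who takes 40mg to month 24 but is coded as placebo breaks that condition unless 40mg is inert. Any benefit from 40mg stays in the numerator while these people leave the denominator.

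Elsewhere the SAP treats 40mg as active drug: definition (ii) codes it as intervention, and Section 9 has a 40mg-only simvastatin group. The two definitions together show how far the result depends on the coding of 40mg. The separate triggers can remove one of them, and it is always (ii). What remains is then compared with the -3 margin under a description that does not mention the assumption.

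**Working it through.** **The plan's own figure.** SAP 4.2 uses a "two-sample t-test with a 10% one-sided alpha", SD 7.5, and a null hypothesis that the simvastatin mean change "is at least 3 points less" than the placebo mean change, with 57 per group "to provide 80% power to reject the null hypothesis of non-futility and declare futility".
- n = 2 × (1.2816 + 0.8416)² × 7.5²/3² = 56.4, so 57 per group (exact t-test power 80.1%).
- 57/(1 − 0.15)² = 78.9, so 79.
- 79/(1 − 0.20) = 98.75, so 99 per group and 198 in total.

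All four figures reproduce. Below I use 79 per arm with 24-month data (99 × 0.80 = 79.2).

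**Nesting.** The (ii) list (discontinued, out of window) is contained in the (i) list (the same two plus remaining on 40mg). Hence (ii) cannot reach 20% unless (i) does, but (i) can reach it alone. This holds whichever denominator is used for the 20%.

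**Algebra, setting visit timing aside.** Let p80 and p40 be the shares of the simvastatin arm on each dose to month 24, D the 80mg effect and kD the 40mg effect.
- Arm difference = D(p80 + k·p40)
- CACE(i) = arm difference/p80 = D(1 + k·p40/p80)
- CACE(ii) = arm difference/(p80 + p40)

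For k between 0 and 1, (i) is at or beyond D in size and (ii) is at or short of it, so the pair brackets the 80mg effect.

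**Size.** The SAP gives no p40, p80 or k, so these are assumptions. In every row only (i) is triggered.

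| p80 | p40 | Off drug | Non-compliant (i) / (ii) | CACE(i)/D, k = 0.5 | CACE(i)/D, k = 1 |
|---|---|---|---|---|---|
| 0.80 | 0.05 | 0.15 | 20% / 15% | 1.03 | 1.06 |
| 0.75 | 0.10 | 0.15 | 25% / 15% | 1.07 | 1.13 |
| 0.70 | 0.15 | 0.15 | 30% / 15% | 1.11 | 1.21 |
| 0.70 | 0.20 | 0.10 | 30% / 10% | 1.14 | 1.29 |
| 0.66 | 0.19 | 0.15 | 34% / 15% | 1.14 | 1.29 |

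**Effect on the futility test.** The standard error of the arm difference is 7.5 × √(2/79) = 1.193. Testing a CACE against -3 is approximately testing the arm difference against -3 × (share coded treated), at one-sided 10%. Take 0.70/0.20/0.10 and a true effect of -2.
- (i), k = 1: arm difference -1.8, estimate -1.8/0.70 = -2.57. Compared with -2.1, (0.3)/1.193 = 0.25, so futility is declared in about 15% of trials.
- (ii), k = 1: estimate -1.8/0.90 = -2.00. Compared with -2.7, (0.9)/1.193 = 0.75, so about 30%.
- (i) if 40mg is inert (k = 0): arm difference -1.4, estimate -2.00. Compared with -2.1, (0.7)/1.193 = 0.59, so about 24%.

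Of the fall from 30% to 15%, the step from 30% to 24% is the wider standard error under (i); the step from 24% to 15% is the coding. With k = 1, a true -2.6 gives -2.6 × 0.90/0.70 = -3.34, past the margin.

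**Simulation check** (20,000 runs, 79 per arm, 0.70/0.15/0.15, k = 1). A true -2.5 averages -3.04 under (i) and -2.50 under (ii), with futility declared in 9.8% and 17.6%. With no drug effect both average about 0 (68% and 80%), so that gap is precision alone.

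**How wide the (i)-only case is.** Out-of-window visits count towards both triggers. If missing the window is independent of stopping, 10% off drug reaches 20% under (ii) when w of those still treated miss it: 0.10 + 0.90w = 0.20, w = 11%. With 15% off drug, 0.15 + 0.85w = 0.20, w = 6%. Beyond those rates both CACEs run.

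**The case against.** A reader might infer that the report would contain only an analysis that counts 40mg as no drug, or that the trial's conclusion is tilted. The SAP does not support either. The primary analysis (3.3, 7.2) keeps participants who began the higher dose and later stepped down in their allocated arm, and it is always reported with its 80% interval. The decision rule in 7.2.1 rests on that test and names secondary outcomes and safety, not the CACE, as further inputs.

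Nor can one say that definition (i) always overstates. There is no inflation if the drug, or 40mg, has no effect, and the factor enlarges a harm as readily as a benefit.

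The missing analysis is also partly recoverable. 7.3.1 reports non-compliance percentages for both definitions, so CACE(ii) is roughly CACE(i) × p80/(p80 + p40). When (ii) is below 20%, the arm difference in the CACE sample is more than 80% of CACE(ii), ignoring statin use in the placebo arm. This gives a crude point estimate, not the covariate-adjusted estimate, its interval or the test.

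Definition (i) can be defended as aiming at the 80mg regimen. The target is legitimate, but the estimator reaches it only if 40mg is inert, and 7.3.1 does not say so. Definition (ii) is not clean either: both definitions code fully treated simvastatin participants seen outside the window as placebo. That is a reason to show both, not to prefer one.

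**Conclusion.** The point holds within limits. It arises only when (i) is at or above 20% while (ii), out-of-window visits included, is below 20%. Then the only CACE reported equals the 80mg effect solely on the unstated assumption that 40mg has no effect. If 40mg acts in the same direction as 80mg, the inflation is about 3% to 29% over the dose shares in the table and k of 0.5 to 1, all assumed. For a beneficial drug it makes 'not futile' more likely in that analysis. The consequence is confined to a conditional sensitivity analysis and leaves the primary test untouched. It deserves correction because the reporting rule is one-sided and the claim of no bias is unconditional.

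**What to change.** In 7.3.1, and to match in 3.3 and 4.4.2, replace the definition-by-definition trigger with a statement that if either definition reaches the trigger, the CACE under both definitions will be reported side by side.

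Replace the description of the CACE as unbiased with its assumptions: (i) assumes that 40mg has no effect; (ii) counts 40mg as full treatment; both assume no drug effect in simvastatin participants coded as placebo, including those seen outside the 2-week window.

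The cost is a few lines of SAP text and one extra model on existing data. No dose or clinical rule changes.

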- (ii) Participants are compliant if they take and maintain 80mg or 40mg and attend the 24 month follow-up visit within the 2-week window of their due date, and non-compliant if they attend their 24-month follow-up outside of the 2-week window or discontinue trial treatment.

[figure not shown]

Figure 1: Possible scenarios for non-compliance during the PD Stat study. Where 24m = 24 months and 2w = 2 weeks. Blue solid line boxes denotes compliance with the study protocol; the yellow dashed boxes denotes participants who may be considered as compliers or non-compliers depending on whether definition (i) or (ii) for compliance is used; the red dotted line boxes represents non-compliance.

The number and proportions of participants classified as non-compliers, as defined above, will be summarised for each allocated group separately and overall, alongside details of the non-compliances. A formal complier-average causal effect (CACE) analysis will proceed if at least 20% of participants in the Simvastatin group are classified as non-compliers according, in turn, to each of the definitions above. Whilst non-compliance rates will be calculated and presented for participants allocated to the placebo group as well as participants allocated to the intervention group, their compliance is not relevant to the one-sided CACE analysis, in which non-compliance to the placebo/control does not imply receipt of the active intervention.

There are no planned protocol deviations. Any unintended protocol deviations will be documented and reported to the Chief Investigator and Sponsor. The number of deviations and percentage (number) of participants with protocol deviations will be reported.

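### The CACE codes treated simvastatin participants seen outside the month-24 window as given placebo, which biases it when the drug has an effect and weakens its futility test

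*SAP*

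**What the plan says.** SAP section 4.4.2 gives two definitions of compliance. Under (i), participants are "non-compliant if they remain on the 40mg dose, discontinue trial treatment or attend the 24-month follow-up visit outside of the 2-week window". Under (ii), staying on 40 mg is accepted, but participants are "non-compliant if they attend their 24-month follow-up outside of the 2-week window or discontinue trial treatment". Both definitions therefore combine drug receipt with visit timing.

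Section 7.3.1 uses these definitions to build the endogenous variable of an instrumental-variable model, with allocation as the instrument. For a simvastatin participant who misses the month-24 window under definition (i), the operative clause is "within the 2-week window, they would be classed as non-compliers and their given treatment would be classified as placebo". Definition (ii) has the same effect: anyone who fails it becomes placebo. Non-compliant placebo participants stay placebo, apart from the external-statin exception.

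Section 7.3.1 describes the CACE as an analysis "which will provide an unbiased estimate of the intervention effect, based on protocol compliance", and its result is read against the same one-sided futility hypothesis as the primary analysis. The CACE runs only if non-compliance reaches 20%. No version based on drug receipt alone is planned.

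**The concern.** In an instrumental-variable analysis, allocation may affect the outcome only through the treatment recorded as received. A participant who maintained 80 mg for 24 months and was assessed three weeks late did receive the drug. If that person is coded placebo, any drug effect stays in the numerator (the allocation effect) while the person is removed from the denominator (the treated share). The exclusion restriction then fails unless the drug has no effect in such participants.

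The coding also disagrees with a neighbouring rule. In section 7.3.1 a placebo participant with at least 21 months on an external statin judged equivalent counts as intervention, and no visit window is stated. A simvastatin participant with about 24 months of study drug and an off-window visit counts as placebo.

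Off-window visits are foreseeable. Section 2.3 has visits rescheduled when rescue medication was taken, and section 4.4.2 names difficulty attending in the OFF state. They also count toward the 20% trigger. With the planned 15% stopping drug, a further 5% treated but off-window would reach it.

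At stake is whether the CACE, when it runs, estimates what the SAP claims, and whether its futility test is needlessly weak.

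**Working it through.** **Inputs from SAP section 4.2.** Test: "The sample size calculation was based on a two-sample t-test with a 10% one-sided alpha". Sample size: chosen "to provide 80% power to reject the null hypothesis of non-futility and declare futility". Margin: under the null, the simvastatin mean change "is at least 3 points less (as higher MDS-UPDRS scores are worse) than the corresponding mean change in the placebo group", so −3. SD: "we assume a slightly inflated standard deviation over this period of 7.5 points". Stopping in the simvastatin arm: 15%. Loss to follow-up: 20%.

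**The plan's own figures reproduce.** n = 2 × (1.2816 + 0.8416)² × 7.5² / 3² = 56.35, so 57 per group. 57 / 0.85² = 78.9, so 79. 79 / 0.8 = 98.75, so 99 per group and 198 in total. About 99 × 0.8 = 79 per arm are then expected with 24-month data, and SE_ITT = 7.5 × √(2/79) = 1.193.

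**What the coded ratio estimates.** Let s_in be the share of the simvastatin arm treated and in window, and s_off the share treated but off-window. Let Δ_in and Δ_off be the drug effects in these two groups, with no effect in those who stopped.

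- Allocation effect: ITT = s_in Δ_in + s_off Δ_off.
- SAP ratio: ITT / s_in = Δ_in + (s_off / s_in) Δ_off.

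The second term vanishes only if Δ_off = 0. If both groups share one effect Δ, the ratio is Δ × (s_in + s_off) / s_in.

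**Futility test.** With c the share coded as treated, CACE = ITT / c and SE = SE_ITT / c, so z = (CACE + 3) / SE = (ITT + 3c) / SE_ITT. At one-sided 10%, futility is declared when ITT > −3c + 1.2816 × 1.193 = −3c + 1.53. Lowering c by s_off raises this cut-off by 3 × s_off. Since z can only fall, a conclusion can change only from futile to not futile.

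**Range.** 15% stopped drug (planning figure). The off-window shares of the arm are assumed. Coding by drug receipt gives c = 0.85, cut-off −1.02 and power 0.80 at zero effect.

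| Treated but off-window | c as coded | Inflation factor | ITT cut-off | Rise in cut-off | Power at zero effect |
|---|---|---|---|---|---|
| 5% | 0.80 | 1.06 | −0.87 | 0.15 | 0.77 |
| 10% | 0.75 | 1.13 | −0.72 | 0.30 | 0.73 |
| 15% | 0.70 | 1.21 | −0.57 | 0.45 | 0.68 |
| 20% | 0.65 | 1.31 | −0.42 | 0.60 | 0.64 |

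**Example at 15% off-window, ITT = −0.8.**

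- Drug-receipt coding: CACE −0.94, SE 1.40, z = (−0.8 + 2.55) / 1.193 = 1.47, p = 0.071, 80% CI −2.74 to 0.86. Futile.
- SAP coding: CACE −1.14, SE 1.70, z = (−0.8 + 2.10) / 1.193 = 1.09, p = 0.138, 80% CI −3.33 to 1.04. Not futile.

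The lower limit moves by 0.59: about 0.20 from the estimate and 0.39 from the wider interval. At 5% off-window the cut-off is −0.87, so the same ITT would still give futility.

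**Simulation** (two-stage least squares, 8,000 runs, 79 per arm, SD 7.5, 15% stopped, 15% off-window). True effects in takers of −3, −2 and −1 are estimated as −3.67, −2.45 and −1.21. The conclusion changes in 5.3%, 11.0% and 15.4% of trials, with no change in the other direction. At zero effect there is no material bias, but futility is declared in 0.69 of trials instead of 0.81.

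**The case against.** The strongest reply is about reach. The CACE is a conditional sensitivity analysis, run after the primary analysis and once the statistician is unblinded. The primary result and the recommendations in section 7.2.1 rest on Equation 2 in the mITT sample. This stands. A reader might infer that late visits could overturn the trial's futility conclusion, but nothing in the SAP lets the CACE replace it.

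A reader might also infer that the coding drives the estimate to or past −3, or that it could discard an effective drug. Neither follows. In the example the estimate moves only from −0.94 to −1.14, and most of the change in conclusion is lost precision. Rejecting non-futility becomes harder, so the coding does not raise the type I error that section 4.2 defines as losing an effective treatment. If simvastatin looked worse than placebo, the estimate would move away from −3.

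The size is uncertain too, because the SAP gives no off-window share. At 5% the cut-off moves by only 0.15 points.

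It can be argued that the target is protocol compliers, visit timing included. That does not rescue the estimate: treated off-window participants still put their drug effect in the numerator, so the ratio is not the effect in in-window compliers. Drug may have ended at month 24 before a late visit, but slight dilution of exposure is not placebo.

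On 40 mg, definition (ii) already gives the lenient version. What remains is that definition (i) should state its assumption of no effect at 40 mg.

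**Conclusion.** The point holds as a flaw in a conditional sensitivity analysis and should be fixed. Both definitions understate the treated share. If the drug has a non-zero effect in treated but off-window participants, the exclusion restriction fails and the CACE is not unbiased as claimed. With a common effect among takers it is inflated by 1.06 to 1.31 for off-window shares of 5% to 20%. With no effect in those participants there is no bias from this source, but power still falls, for example from 0.80 to 0.68 at 15%.

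The direction follows from the stated rule. The size rests on the assumed off-window shares, 15% stopping, 79 per arm, SD 7.5, no coded treatment in the placebo arm, and the normal approximation. The primary mITT test is unaffected.

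**What to change.** - For the CACE and its 20% trigger, define given treatment from drug receipt only (dose maintained to month 24, from self-report and capsule counts), and drop the visit-window condition from both definitions. Definition (i) also selects participants for the disease-modifying analysis in section 7.4.2, so confine the change to the CACE.
- Examine visit timing separately in both arms, for example with actual time since baseline added to Equation 2, noting that it is measured after randomisation. Dropping off-window visits should not be the main approach, since section 7.3.1 rejects per-protocol analysis because it excludes participants after randomisation.
- Replace the claim of an unbiased estimate with the assumptions needed, including that definition (i) assumes no effect of 40 mg.
- The last revision in SAP v2.1 was made with group allocations revealed. Label this change as post-unblinding and report the new CACE beside the pre-specified one.

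The cost is SAP wording, a recomputed compliance flag, additional model runs and disclosure of the timing. No new data are needed.
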